The primary outcome is tobacco use (Yes/No, defined as active use in the last 7 days) and the secondary outcome is the presence of surgical complications (classified into respiratory, cardiovascular, wound complications, and mortality).

The specific objectives are the following:

To compare the effectiveness of the intervention in terms of abstinence, patient evolution, motivation and the attempts to quit smoking between the patients in the IG and the CG undergoing one of the two types of surgery.To compare the length of hospital stay (in days) and the number of re-admissions between the IG and the CG according to type of surgery.To compare surgical and post-surgical complications and mortality rates between the IG and the CG up to 90 days post-surgery.To assess whether the intervention can be implemented in the health system in Spain.

These objectives will be analyzed by comparing the results obtained in the IG and CG at the following time points: before surgery (at the beginning of the study), on the day of surgery, and at 1, 3, 6 and 12 months post-surgery (Table 1).

**Table 1 t0001:** Plans for assessment and collection of different variables in surgical patients who participate in the RCT at the Vall d´Hebron University Hospital, Barcelona (N=232)

*Variables*	*Baseline*	*Day of* *surgery*	*1 month* *post-surgery*	*3 months* *post-surgery*	*6 months* *post-surgery*	*12 months* *post-surgery*	*Re-admission*
Sociodemographic data	x						
Specialty	x						
Type of SI	x						
Smoker (yes/no)	x	x	x				
Type of consumption	x						
Amount of consumption	x	x	x (if s)	x (if s)	x (if s)	x (if s)	
Fagerström test	x		x (if s)	x (if s)	x (if s)	x (if s)	
Stages of change	x		x (if s)	x (if s)	x (if s)	x (if s)	
Richmond test	x		x (if s)	x (if s)	x (if s)	x (if s)	
Previous abstinence	x						
Previous drugs	x						
Living with smoker	x						
Comorbidities	x						
General self-efficacy scale	x						
CO-oximetry		x					
ASA PS classification		x					
ATB prophylaxis		x					
Duration of surgery		x					
Blood transfusion		x					
SatO2 at start of surgery		x					
Complications of surgery		x					
Complications at time of recovery room care discharge after surgery		x					
Attempts to quit			x (if s)	x (if s)	x (if s)	x (if s)	
Decrease in consumption			x (if s)	x (if s)	x (if s)	x (if s)	
Pharmacological treatment			x	x	x	x	
Is lack of NRT funding a problem?			x	x	x	x	
Readmission (yes/no)							x
Reason for readmission							x
SSI							x

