### Study population

The study population will be adult patients scheduled to undergo the following surgeries at the Orthopedic Surgery and Traumatology, General Surgery and Urology services at the Vall d’Hebron University Hospital in Barcelona: knee replacement, hip replacement, instrumented spinal arthrodesis, anterior cruciate ligament repair, colorectal surgery for colon and rectal neoplasia, cystectomy, radical prostatectomy and partial or radical nephrectomy. The inclusion criteria are: adults aged ≥18 years; conscious and oriented in space, time and person; scheduled for surgery at least four weeks after inclusion in the surgical schedule; daily and occasional smokers (occasional: do not smoke every day); resident in the healthcare area and have no plans to change address in 12 months. The exclusion criteria are: pregnancy; smokers already undergoing treatment to stop smoking; inability to give informed consent due to memory loss or insufficient understanding of Spanish or Catalan; non-primary nature of knee or hip replacement; scheduled to participate (or already participating) in a clinical trial in which nicotine replacement therapy (NRT) is an exclusion criterion.

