### Data analysis

The implementation of the intervention will be evaluated with data on fidelity, dose and scope with respect to the protocol (time spent on visits, use of instruments, barriers and problems detected, recruitment of participants, adherence to treatment, satisfaction). This stage will be carried out prior to the analysis of the results of the RCT. The efficacy of the intervention in terms of abstinence and post-surgical complications will be evaluated by comparing IG and CG. The data will be analyzed separately in the two surgery groups (orthopedic with implants and general/urological). Using the data obtained at the beginning of the study (i.e. a questionnaire with baseline data on tobacco consumption and sociodemographic variables) and the data from the different assessments over the course of the study, descriptive analyses will be performed and a contingency table with bivariate analysis will be created. Logistic regression will be performed to assess the efficacy of the intervention and the rest of the outcome variables. As part of our secondary analyses, we will explore whether the intervention effect varies across different surgical groups by including an interaction term (type of surgery × intervention) in our regression models. Considering the longitudinal nature of our data, a generalized linear mixed binomial family model to account for the correlation between repeated measurements within individuals will be used to assess the evolution of smoking cessation. Hazard ratios (HRs) of surgical complications in the IG and the CG will be calculated using Cox regression models. The proportional hazards assumption will be evaluated using statistical tests (e.g. Schoenfeld residuals) to ensure the validity of the Cox model. The number of patients needed to be treated to achieve cessation in one patient (NNT, and its 95% confidence interval) will be calculated over the one-year period. The NNT is the inverse of the attributable risk and is useful for conveying the efficacy of the intervention to patients, managers and clinicians. All analyses will be performed on an intention-to-treat basis. The level of statistical significance will be set at α=0.05 and the Bonferroni correction will be considered to adjust for multiple comparisons.

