## DISCUSSION

Smoking is a major risk for patients undergoing surgery. Surgical complications are associated with smoking increasing readmission rates, prolonging hospital stays and ultimately increasing healthcare costs.

Smokers scheduled for surgery are at an ideal time to try a quit attempt^32^. Intensive interventions initiated at preoperative visits are known to be effective^17^ and can reduce complications. Despite this evidence, little help in this regard is offered during pre-surgical visits^33^. This study is the first in Spain to evaluate the effectiveness of an intensive pre-surgical intervention comprising psychological and behavioral support, pharmacological therapy, and a one-year follow-up program designed to help patients quit smoking before they undergo surgery.

The sample size and stratification will allow us to perform subgroup analyses, and the one-year follow-up period will enable us to obtain longterm abstinence data comparing CO-oximetry measurements made on the day of surgery and at the end of the study.

The main expected result is the achievement of an abstinence rate that is 15% higher among patients in the IG compared to those in the CG, and, at the same time, a reduction in the risk of complications in the IG. The analyses will also consider sociodemographic variables, comorbidities, type of surgery, and surgical variables such as duration and transfusions required. Other important results for comparison between groups will be motivation, dependence, cessation attempts, and reduction in consumption.

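### Length of stay, readmission and complications are compared within two surgery groups that each pool four kinds of procedure, and the surgical covariates named are post-randomisation ones rather than the baseline procedure, which costs precision.

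*Protocol article*

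**What the plan says.** All references are to the protocol article. Study population lists the eligible operations. Besides joint replacement at the knee or hip, they are "instrumented spinal arthrodesis, anterior cruciate ligament repair, colorectal surgery for colon and rectal neoplasia, cystectomy, radical prostatectomy and partial or radical nephrectomy". Four are orthopedic (knee, hip, spine, cruciate ligament) and four general or urological (colorectal, bladder, prostate, kidney).

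Among the specific objectives in the Introduction, the second compares days in hospital and readmissions "between the IG and the CG according to type of surgery"; the third is worded "To compare surgical and post-surgical complications and mortality rates between the IG and the CG up to 90 days post-surgery". Data analysis then fixes the level of comparison: "The data will be analyzed separately in the two surgery groups (orthopedic with implants and general/urological". For complications it adds "Hazard ratios (HRs) of surgical complications in the IG and the CG will be calculated using Cox regression models", with no covariates listed.

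Three places name covariates:

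- Outcome variables treats surgical time and blood transfusions as possible confounders for complications and mortality.
- Independent variables lists sociodemographic data, among them type of surgery, and comorbidities.
- The Discussion says the analyses will take account of sociodemographic variables, comorbidities, "type of surgery, and surgical variables such as duration and transfusions required".

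Table 1 has two separate baseline rows, one for specialty and one for type of SI (surgical intervention). Methods calls the trial stratified, with 58 patients per arm in each surgery group, and names no finer stratum.

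**The concern.** Length of stay and complication risk plausibly differ between, say, cruciate ligament repair and spinal arthrodesis, or between prostatectomy and cystectomy. If they do, variation between procedures goes into the error term of every within-group comparison and widens the intervals for the second and third specific objectives.

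The named covariates do not deal with this. Type of surgery, where its meaning can be checked, has two levels: the first specific objective speaks of two types, and the interaction in Data analysis is across surgical groups. A two-level variable is constant within each group.

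Surgical time and transfusions are measured during the operation, after randomisation. They cannot confound a randomised comparison, and adjusting for them risks removing part of any effect of the intervention. The procedure is fixed before randomisation and appears to be collected already.

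**Working it through.** **The plan's own figures.** No precision or power figure is given for length of stay, readmission or complications. The only usable input is n = 58 per arm within a surgery group (4 × 58 = 232, as stated). Stays, risks and case mix by procedure are not in the documents. Everything below assumes them, with four equally frequent procedures per group.

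**Chance imbalance.** For a procedure with share q of a group, the SD of the between-arm difference in share under simple randomisation is √(2q(1−q)/n). With q = 0.25 and n = 58 this is √(0.375/58) = 0.080, so the 95% range is ±1.96 × 0.080 = ±15.8 points. For q between 0.10 and 0.50 the range is ±10.9 to ±18.2 points.

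**Length of stay.** Let B be the between-procedure variance and W the within-procedure variance. Then R² = B/(B + W), and the interval narrows by 1 − √(1 − R²).

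| Assumed stays | Within-procedure SD | R² |
|---|---|---|
| means 3/4/4/5 days | 3 days | 0.5/9.5 = 0.05 |
| means 3/4/7/10 days | 4 days | 7.5/23.5 = 0.32 |
| means 1/4/4/6 days | 2.5 days | 3.19/9.44 = 0.34 |
| means 2/4/8/15 days | 4 days | 24.7/40.7 = 0.61 |
| medians 4/5/6/9, log scale | 0.8 to 0.4 | 0.12 to 0.36 |
| medians 2/3/4/5, log scale | 0.8 to 0.4 | 0.15 to 0.42 |
| medians 3/4/7/14, log scale | 0.8 to 0.4 | 0.35 to 0.68 |
| medians 1/4/4/6, log scale | 0.8 to 0.4 | 0.42 to 0.74 |

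At R² = 0.05 the interval narrows by 1 − √0.95, about 3%. At R² = 0.74 it narrows by 1 − √0.26, about 49%. In days, the standard error goes from 0.57 to 0.56 in the first row and from 1.18 to 0.74 in the fourth.

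**Complications, risk-difference scale.** Let p be the mean risk and B the variance of the procedure risks. The unadjusted 95% half-width is 1.96√(2p(1−p)/58). With mix removed it is 1.96√(2[p(1−p) − B]/58).

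- Risks 10/15/30/60%: p = 0.2875, p(1−p) = 0.2048, B = 0.0380. The half-width goes from 16.5 to 14.9 points, 10% narrower.
- Risks 10/15/25/40%: p = 0.225, p(1−p) = 0.1744, B = 0.0131. The half-width goes from 15.2 to 14.6 points, 4% narrower.

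A more extreme set, 5/10/25/60%, has R² = 0.247 and gives 1 − √0.753, about 13%.

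The part of the sampling error due to mix, 1.96√(2B/58), is ±7 points for the first set and ±4 for the second. It is already inside the unadjusted half-width and does not add to it.

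**Validity of the unadjusted test.** In 10,000 simulated trials with no effect (normal stays, means 2/4/8/15 days, SD 4, 58 per arm, simple randomisation), the unadjusted t-test rejected in 4.9% at a nominal 5%.

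No calculation was made for readmission.

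**The case against.** The strongest reply is that this is silence in a condensed article. Covariate lists usually sit in the analysis plan, which is not shown, and the strata of the randomisation are not spelled out. Type of surgery in Independent variables and in the Discussion might mean the procedure itself, since a two-level variable would be idle within a group. That ambiguity is real, and it rules out saying that the plan ignores case mix: type of surgery and comorbidities are both listed for consideration. But the article is not merely silent. It chooses surgical covariates, and the two that it names unambiguously arise after randomisation. If the procedure was a randomisation stratum after all, it would still belong in the model.

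A reader might infer that a chance excess of one major procedure would bias the result or pass for an intervention effect. The documents do not support that. Randomisation keeps the unadjusted comparison unbiased, and the confidence interval already allows for chance differences in mix.

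Two further objections stand. The gain for complications is small even under risks chosen to differ widely. The gain for length of stay rests wholly on assumed stays. Sparse strata are also a fair worry: 58/4 is about 14 patients per arm per procedure with an equal mix.

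**Conclusion.** The point holds as a loss of precision on secondary outcomes. Within each surgery group nothing clearly named in the plan adjusts for procedure, and the surgical covariates clearly named are post-randomisation ones.

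Under the assumed values, procedure explains about 5% to 74% of the variance in length of stay, so the gain from adjusting runs from negligible to large. For complications the interval narrows by about 4% to 10% on the risk-difference scale under the two main risk sets. In a Cox model the gain appears differently: adjustment tends to move the hazard ratio away from 1 rather than shorten its interval, and the hazard ratio becomes one conditional on procedure.

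The conclusion assumes that the Table 1 row for the surgical intervention records the individual procedure, which its separation from specialty suggests but does not prove. The documents do not support the stronger readings that the comparison is invalid or that the procedures have known, very different stays and risks. The primary abstinence outcome is not affected.

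**What to change.** In Data analysis and in the Discussion, name the procedure recorded at baseline (the 'Type of SI' row of Table 1) as the prespecified surgical covariate for length of stay, and as a covariate or stratum for complications and readmission. State the merging rule for rare procedures in advance, for example hip with knee replacement. Say whether type of surgery means the two groups or the procedure.

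In the models that estimate the intervention effect, use this variable in place of surgical time and transfusions, and amend Outcome variables to match. Those two can still be reported descriptively by arm.

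The cost is wording, a few degrees of freedom and some merging of sparse procedures. No new data are needed. With 25 patients recruited according to Current status of the RCT, the choice can still be made before any imbalance is seen.

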### Outcome variables

The main outcome variable will be tobacco use (Yes/No, defined as active use in the last 7 days)^25^ at the various time points. Abstinence validation will be performed with CO-oximetry on the day of surgery and at 12 months for subjects who declare themselves abstinent (patients with CO >6 ppm will be considered as active smokers)^26^. At the other time points (start of the study, and at 1, 3, 6 and 12 months) abstinence will be self-reported by the patient. The following secondary variables will be recorded at each assessment: 1) type of tobacco product (cigarettes, rolling tobacco, cigars, etc.); 2) pattern of consumption of each type of tobacco product (daily or occasional, and daily/weekly amount); and 3) level of nicotine dependence, using the Fagerström test (low 0–3, medium 4–6, and high 7–10)^27^. Other variables that will be assessed include motivation and self-efficacy, willingness to quit smoking according to the Prochaska and Di Clemente model^28^, level of motivation using the Richmond test^29^; and the General self-efficacy scale (based on Bandura’s social cognitive theory)^30^.

Another outcome variable will be surgical complications classified into the following groups and assessed on the day of surgery, on discharge from recovery-room care, hospital discharge, and up to 90 days post-surgery: 1) respiratory complications (bronchospasm, respiratory failure requiring oxygen and active treatment, respiratory superinfection requiring antimicrobial treatment, pleural effusion, other); 2) cardiovascular complications (deep venous and pulmonary thromboembolic disease, hypertensive crises, angina, new onset arrhythmias/blockages, acute myocardial infarction, heart failure, other); 3) postoperative complications of the surgical wound (dehiscence, fistula or infection of the internal or deep wound, seroma, wall abscess or fistula of the external wound with antimicrobial treatment and positive cultures, other); and 4) mortality (during hospitalization and within 90 days of surgery). All complications after the day of surgery will be recorded taking into account data from the patient’s medical history. Variables related to surgery: surgical time, blood transfusions (to be assessed as possible confounding variables for post-surgical complications and mortality). Variables related to hospital care: length of hospital admission (in days); and readmissions required within 12 months of hospital discharge.

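### Logistic regression is assigned to all remaining outcomes, but length of stay is in days; readmission is defined two ways and complications fall under two models

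*Protocol article*

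**What the plan says.** The Data analysis section gives a general rule: "Logistic regression will be performed to assess the efficacy of the intervention and the rest of the outcome variables". It names two other models. One is "a generalized linear mixed binomial family model to account for the correlation between repeated measurements within individuals", which is for the course of smoking cessation. The other is for complications: "Hazard ratios (HRs) of surgical complications in the IG and the CG will be calculated using Cox regression models", with a check of proportional hazards.

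The outcomes to which the rule would apply are defined elsewhere:

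- **Stay and readmission.** One specific objective in the Introduction is "To compare the length of hospital stay (in days) and the number of re-admissions between the IG and the CG", according to type of surgery. The Outcome variables section lists "length of hospital admission (in days); and readmissions required within 12 months of hospital discharge". Table 1 has a row for readmission as yes/no and no row for a number of readmissions.
- **Complications.** The Introduction names as secondary outcome whether surgical complications are present, in four classes of which mortality is one. Outcome variables says they are "assessed on the day of surgery, on discharge from recovery-room care, hospital discharge, and up to 90 days post-surgery".

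No cut-point for stay is given, and no linear, count or duration model is named for stay or readmissions.

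**The concern.** The article does more than leave the model for stay open: it names one, and that model does not suit the scale on which stay is defined. Following the sentence as written means splitting days at some value. That treats, say, a stay one day above the cut and a stay of several weeks as the same result, and the value can be picked after the data are seen.

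For readmissions, the right model depends on which definition holds. Logistic regression suits the yes/no item in Table 1 but not the number in the objective.

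For complications, the general logistic sentence and the specific Cox sentence can both be read as covering the same outcome. Two candidate analyses of the named secondary outcome, neither marked as the main one, allow a choice between an odds ratio and a hazard ratio once results are known.

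**Working it through.** **1. Models against scales.** The plan states no figure on this point, so there is none to reproduce. Setting the sections side by side:

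| Outcome | Scale in the article | Model that the text assigns | Fit |
|---|---|---|---|
| Length of stay | Days (objectives; Outcome variables) | Logistic, as a remaining outcome | Only after an unstated cut |
| Readmission | Number (objectives); yes/no (Table 1) | Logistic, as a remaining outcome | Fits the yes/no item, not the number |
| Complications | Present or not, followed to 90 days | Logistic (general sentence) and Cox (specific sentence) | Either can be used; main one not named |
| Abstinence | Yes/no | Logistic; binomial mixed model over time | Fits |

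**2. Group sizes.** From Sample size and randomization: 232 in total, 58 in each of four groups. Combined over surgery types, an arm has 2 × 58 = 116. The Data analysis section analyses the two surgery groups separately, so 58 per arm applies there.

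**3. What a cut of stay costs (illustration).** For a normal outcome, for example log days, a median split keeps 2/π = 0.637 of the information. Then 116 × 0.637 = 74 and 58 × 0.637 = 37 effective patients per arm. This is a general large-sample value, not a property of this trial.

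A simulation with assumed inputs gives the same picture. Stay is log-normal, rounded up to whole days, with medians 5 and 4 days and log-SD 0.6, in 4,000 simulated trials:

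| Per arm | t-test on log days | Chi-square after median split |
|---|---|---|
| 58 | 51% | 35% |
| 116 | 79% | 63% |

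The loss is about 16 percentage points in both rows. The simulation error is at most √(0.5 × 0.5 / 4000) = 0.8 points. The documents give no distribution of stay, so the size is illustrative; the direction does not hang on the chosen values.

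**4. Logistic or Cox for complications (illustration).** Assumed: 90-day risk 30% against 20%, 116 per arm, and a share of events on the day of surgery varied over 10%, 30% and 50% (400 simulated trials each).

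| Share on day of surgery | Cox, these events kept at 0.5 day | Logistic, 90-day yes/no | Cox, time-zero patients dropped | Patients dropped |
|---|---|---|---|---|
| 10% | 43% | 43% | 41% | 6 |
| 30% | 40% | 42% | 35% | 17 |
| 50% | 39% | 39% | 22% | 29 |

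The simulation error is about √(0.4 × 0.6 / 400) = 2.4 points, so the first two power columns are indistinguishable. Cox loses power only if patients with time zero leave the analysis, and nothing in the article plans that.

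**The case against.** The article is a condensed account. Its authors may have meant the logistic sentence for binary outcomes only, with other scales left to a fuller plan. The Cox sentence is specific and can be read as overriding the general one for complications. Table 1 records readmission as yes/no, which logistic regression handles with no arbitrary cut. All of this concerns secondary outcomes.

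Much of that is fair. For readmission, the fault is the conflict between the objective and Table 1, not the model as such. For complications, naming the main analysis is enough. The argument does not rescue length of stay: days is the stated scale in two sections, the sentence takes in every remaining outcome, and no alternative is named.

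A reader might infer three stronger points, which the documents do not support:

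- **That Cox regression does not fit complications because some occur in theatre or in the recovery room.** The article states no time origin. Randomisation follows the baseline call and precedes a first visit about four weeks before surgery (Procedure; Components of the intensive intervention), so a randomisation origin gives every event a positive time. With surgery as origin, events on the same day can be handled as ties or given a small positive time. A proportional-hazards check is planned. Dropping time-zero records is a matter of software handling, and the article ties Stata only to the sample size and the allocation sequence.
- **That deaths would be censored.** The Introduction and Outcome variables both make mortality one of the complication classes. Censoring by death would arise only in separate models for the other classes, which the article does not describe.
- **That the trial loses 36% of its information on stay.** No median split is planned, so the 64% efficiency figure only illustrates the cost of a cut.

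**Conclusion.** The point holds for length of stay: the stated rule forces a dichotomy that the article does not define, loses information and leaves the cut to be chosen later. Under the assumed distribution the cost is about 16 points of power. That size rests on the assumed medians, spread and median split.

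Two smaller inconsistencies stand with it. Readmission is a number in one place and yes/no in another, and complications have two possible models without a stated main one. Cox regression is usable for complications once its time origin keeps the day-of-surgery events.

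Only secondary outcomes are touched. The abstinence analysis and the sample size of 232 do not change.

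**What to change.** - **Length of stay:** analyse in days with a model for a skewed duration, for example log-linear or negative binomial regression. Choose one in advance and include type of surgery. Limit the logistic sentence to binary outcomes.
- **Readmission:** reconcile the objective with Table 1. Either declare readmission within 12 months binary and keep logistic regression, or record the number and use a count model.
- **Complications:** name one main analysis, preferably the 90-day risk including day-of-surgery events, with mortality counted as the article already defines it. Keep Cox as supportive and state a time origin under which day-of-surgery events stay in the analysis.

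The cost is mostly wording. Counting readmissions may need a small change to the data form, since Table 1 shows only yes/no. The article reports 25 subjects recruited at the time of writing, so at that stage all of this could be fixed before outcome data were compared.
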